### Sample size analyses

Mehr and colleagues [25] estimated that the incidence of nursing home-acquired pneumonia in the United States may range between 0.3 to 2.3 episodes per 1,000 resident-days. In the present study, we expect to enroll 800 EHPAD residents and follow them over a 12-month period (i.e., a total of 292,000 resident-days). Considering the attrition due to mortality (i.e., 20% per year in this setting^4^), we may expect between 70.1 and 537.3 cases according to the Meher and colleagues’ data [25]. More recently, Rothan-Tondeur and colleagues [38] reported 311 infections in a sample of 2,140 nursing home residents over a period of 28 days (from January 24 to February 20, 2005). The study was conducted defining pneumonia according to the same criteria we will implement in INCUR. Authors showed that pneumonia represented the 7% of all the cases of infections (i.e., 22 events). Translating these figures over a 365-day period (as proposed in the INCUR project) and sample size we plan to recruit (i.e., 800 participants), we obtain 107.2 pneumonia events. It might happen that attrition due to mortality (i.e., 20% per year^4^) and the spring-summer seasons (during which the pneumonia events might be fewer; i.e., additional 40% over 6 months) may further reduce such estimation. However, we believe that, even in the worst case scenario (i.e., 68.6 cases of pneumonia over one year, consistent with the minimum estimation obtained from analyses performed on the Meher and colleagues’ data [25]), it will be possible the evaluation of a sufficient number of events to successfully accomplish the INCUR study aims. The recruited sample size of 800 participants produces a two-sided 98.2% or 95.2% confidence interval with a width equal to 0,050 when the incidence of pneumonia are 10% or 15%, respectively. Such incidence rates are overestimating the outcome of interest compared to the previous study by Rothan-Tondeur et al [38]. (7%); thus, INCUR study is adequately powered to accurately estimate the incidence of pneumonia with the sample of 800 participants.

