### Analysis plan

All the analyses will consider an alpha value threshold equal to 5% as determining the statistical significance.

Primary aims:

a. Taking into account the 12-month follow-up of the study participants, we will detect all the participants experiencing a new pneumonia event. The ratio between the number of participants experiencing one or more events and the number of participants constituing the overall sample will provide the incidence of pneumonia in the sample population. Results will be presented as pneumonia cases per 1,000 resident-days, and as pneumonia events over one year. Stratified analyses will be performed according to age groups, gender, and pre-existing pulmonary disease.

Secondary aims:

a. Primary independent variable of interest for the present analyses will be the total expenditure (in Euros) that participants will cost to the healthcare system over the follow-up year. Additional secondary analyses will also consider specific aspects of the direct healthcare costs of INCUR participants such as expenses due to hospitalizations or physical therapy sessions. All these analyses will be stratified and compared according to the presence/absence of pneumonia events.

Unadjusted and adjusted analyses of covariance, logistic regression models, and multinominal logistic regression models will be performed to evaluate the means and risks of the outcome variables predicted by the absence/presence of pneumonia events occurred during the follow-up (dicothomous independent variable of interest).

b. Participating patients will be divided in two groups, according to the presence/absence of a pneumonia event experienced during the follow-up period. Then, the risk of death will be calculated and compared between the two groups. Kaplan-Meier survival curves will be provided according to pneumonia events. Moreover, adjusted Cox proportional hazard analyses taking into account age, gender, pre-existing pulmonary disease, and other possible confounders will be performed to estimate the risk of dying in patients who experienced a pneumonia versus those who did not. Follow-up will be censored at the date of death for patients dying during the follow-up, or to the last contact date for those who did not.

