A similar analytical approach will be used to evaluate specific characteristics of the EHPADs as significant determinants of pneumonia events in patients. EHPADs and patients’ characteristics might be combined in secondary analyses to evaluate the additive value of specific parameters towards the onset of pneumonia events.

b. We will perform restricted analyses in participants who will die during the follow-up (expected mortality about 20% over 12 months, that is 160 fatal events in our sample population). This subsample of participants will be divided according to the cause of death (i.e., pneumoniarelated versus other causes [expected number of cases 11.2 versus 158.8 according to Rothan- Tondeur et al [38]). Chi-square and t-test analyses will be performed to verify whether significant differences between patients dying because of a pneumonia event versus those dying for other causes exist for the following healthcare parameters: - Total expenditure (in Euros) that participants will cost to the healthcare system over the follow-up period. This datum will be obtained by the Gerontopôle from the *Caisse Primaire d’Assurance Maladie*, which has allowed the specific and exclusive release of it to the CHUToulouse. Additional analyses will also consider specific aspects of the direct healthcare costs of INCUR participants such as expenses due to hospitalizations or physical therapy sessions.

Mann-Whitney U statistics will be used for non-normally distributed continuous variables. Normalization through log-transformation will be used for non-normally distributed study variables. These analyses will consider the entire follow-up period available. Secondary analyses will also be restricted to consider the last month preceding the fatal event. In this way, we will be able to undestand whether the hypothesized higher healthcare costs of pneumonia events leading to death are distributed over time, or compressed in the very last period of life. If the statistical power will be sufficient, additional adjusted logistic and linear regression models will be performed taking into account potential confounders.

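### Secondary aim a compares mean costs in Euros by ANCOVA with no stated protection against unequal variances; if the small pneumonia group's costs are more variable, a pooled 95% interval is too narrow

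*Protocol article*

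**What the plan says.** Under Analysis plan, Secondary aims, a, the protocol article makes total expenditure in Euros over the follow-up year the main cost measure and compares it by presence or absence of pneumonia. The method is named: "Unadjusted and adjusted analyses of covariance, logistic regression models, and multinominal logistic regression models will be performed to evaluate the means and risks". The section opens with a general rule: "All the analyses will consider an alpha value threshold equal to 5% as determining the statistical significance". Under this aim nothing is said about the form of the standard error, unequal variances, transformation or rank methods.

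The group sizes have to be inferred from Sample size analyses. The total is fixed: "we expect to enroll 800 EHPAD residents and follow them over a 12-month period". From US incidence data the article says "we may expect between 70.1 and 537.3 cases". From a French survey using the same pneumonia criteria it says "sample size we plan to recruit (i.e., 800 participants), we obtain 107.2 pneumonia events", and it then gives a low case: "even in the worst case scenario (i.e., 68.6 cases of pneumonia over one year".

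The cost comparison among residents who die (Tertiary aims, b) is written differently. It names a t-test ("Chi-square and t-test analyses will be performed to verify whether significant differences between patients dying because of a pneumonia event versus those dying") and adds Mann-Whitney and log-transformation for variables that are not normally distributed. Those two provisions appear under the tertiary aims only.

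**The concern.** An ANCOVA with its usual standard error estimates one residual variance from all residents. When one group is much smaller, the larger group supplies nearly all of that estimate. If the smaller group is the more variable one, the pooled figure understates the uncertainty of its mean, and hence of the difference. A larger total sample does not help, because the error depends on the ratio of group sizes and the ratio of variances.

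The plan's own expectations point towards this configuration. Its secondary hypothesis is that pneumonia raises costs. Its Healthcare costs section lists hospital stays, intensive care, intubation and ventilation as markers of cost. Only some residents with pneumonia would incur these, so spread would be expected to rise along with the mean. At stake are the interval and p-value for the main cost difference, which would look more precise than the data justify.

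**Working it through.** **1. The plan's event counts reproduce.**
- Resident-days: 800 × 365 = 292,000.
- US incidence after 20% mortality: 292,000 × 0.8 × 0.3/1,000 = 70.1, and 292,000 × 0.8 × 2.3/1,000 = 537.3.
- French survey: 22/2,140 × 365/28 × 800 = 107.2.
- Low case: 107.2 × 0.8 × 0.8 = 68.6.

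**2. Group ratios**, treating each event as one resident.
- 107.2 events: (800 − 107.2)/107.2 = 6.5, so 1:6.5.
- 68.6 events: (800 − 68.6)/68.6 = 10.7, so 1:10.7.
- A split of 89 v 711 (1:8) lies between these and serves as the worked example.

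Repeat episodes would make the group slightly smaller. If events were Poisson (an assumption), 107.2 and 68.6 events would fall on 800 × (1 − exp(−107.2/800)) = 100 residents and, in the same way, 66 residents.

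**3. Formula.** Set the SD in the no-pneumonia group to 1 and in the pneumonia group to r, with sizes n2 and n1.
- Pooled variance: s² = [(n1 − 1)r² + (n2 − 1)]/(n1 + n2 − 2)
- SE used: √[s²(1/n1 + 1/n2)]
- True SE: √(r²/n1 + 1/n2)
- Coverage: 2Φ(t × SE used/true SE) − 1, with t = 1.963 on 798 degrees of freedom

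**4. Worked case**, 89 v 711 and r = 1.5.
- s² = (88 × 2.25 + 710)/798 = 1.138
- SE used = √[1.138 × (1/89 + 1/711)] = 0.120
- True SE = √(2.25/89 + 1/711) = 0.163
- Ratio = 0.734, and coverage = 2Φ(1.963 × 0.734) − 1 = 85.0%

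**5. Range.** The documents do not give r, so it is assumed.

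| Pneumonia v none | r = 1 | r = 1.25 | r = 1.5 | r = 2 |
|---|---|---|---|---|
| 69 v 731 | 95.0% | 89.8% | 84.2% | 74.5% |
| 89 v 711 | 95.0% | 90.1% | 85.0% | 76.3% |
| 107 v 693 | 95.0% | 90.5% | 85.8% | 77.9% |

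At r = 0.75 (the small group less variable) coverage is 98-99%, so the interval is too wide.

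**6. Upper planning figure.** If 537.3 events are Poisson, they fall on 800 × (1 − exp(−537.3/800)) = 391 residents. For 391 v 409 and r = 2 the formula gives 94.7%. If each of the 537.3 events were a different resident (537 v 263), the pneumonia group would be the larger one and coverage at r = 2 would be 98.4%. The problem therefore belongs to the lower planning figures.

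**7. Skewed costs.** Simulation with lognormal costs (20,000 runs per setting, mean 1.5 times higher with pneumonia) agrees with the formula: for 89 v 711, pooled coverage is 85.6% at r = 1.5 and 77.5% at r = 2. Separate-variance intervals for the same split cover 93.3% and 91.9%. Over the three splits they cover 91-94% at these ratios, and about 95% when costs are normal.

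**The case against.** The strongest reply is that the article never says the variances are assumed equal. It names ANCOVA and stops. It is a condensed account, and the form of the standard error could be fixed in an analysis plan that is not shown. This stands in part: nothing shows that a pooled standard error will certainly be used. But ANCOVA is the method actually named for this outcome, its conventional form pools, and the article gives a provision for awkward distributions under the tertiary aims without giving one here.

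A second reply is that the SD ratio is not in the documents. That is correct. The coverage figures are conditional on it, and an SD ratio of 1 leaves nothing to correct. The upper planning figure removes the imbalance as well. The lower figures remain relevant because the French survey used the study's own pneumonia definition and the article treats 68.6 as its worst case.

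A reader might infer from the same reasoning that the cost comparison among deaths is worse still, since the article expects only 11.2 pneumonia deaths. The documents do not support that. The t-test there may be of the Student or the Welch form; the article does not say. The same paragraph provides Mann-Whitney and log-transformation. On the log scale, if the two distributions differ only by a scale factor, the SD ratio is 1 and the variance problem disappears. Nor do the documents show that costs before pneumonia deaths vary more than costs before other deaths. Welch would not be a full cure in any case: with 11 v 149 and skewed costs it covered only about 85-88% in simulation at SD ratios of 1.5 to 2.

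A reader might also infer that the tertiary provisions would rescue secondary aim a if carried over. They respond to non-normality, not to unequal variance, and neither directly estimates a difference in mean Euros.

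**Conclusion.** The point holds for secondary aim a as a conditional weakness, and it is worth correcting. It is not a demonstrated error: a reader might take the coverage figures as the study's expected performance, but they depend on an SD ratio that the documents do not supply.

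The conclusion rests on four conditions: a conventional ANCOVA on untransformed Euros; a pneumonia group of roughly 69 to 107 out of 800; each event counted as one resident; and more variable costs in that group. Under these, nominal 95% coverage falls to about 90%, 84-86% or 74-78% at SD ratios of 1.25, 1.5 or 2. In terms of the 5% test, the false-positive rate would be about 10%, 14-16% or 22-26% if mean costs were equal but SDs differed by those factors. No coverage claim is made for the comparison among deaths.

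**What to change.** Keep the difference in mean Euros as the quantity to be estimated, and add one sentence under secondary aim a. It should say that the adjusted mean difference will be estimated by linear regression, or by a log-link generalised linear model with the result reported as an adjusted mean difference, and that standard errors will be heteroscedasticity-robust or bootstrapped.

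The cost is one line of wording and slightly wider intervals. If the variances turn out equal, almost nothing is lost. If they differ, the interval widens to reflect the real uncertainty. With strongly skewed costs and about 69 to 107 residents in the smaller group, coverage may still fall a little short of 95%: the separate-variance simulations gave 91-94%.

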### The INCUR study

#### Hypotheses and objectives

The INCUR project is specifically aimed at retrieving data from routine clinical practice in order to estimate the incidence of pneumonia events in older persons living in a sample of French nursing homes. Moreover, INCUR is designed to estimate the clinical and economical consequences of pneumonia events by measuring the subsequent access to medical procedures and resources. More in details, the following hypotheses have driven the rationale and conception of the INCUR project:

Primary hypotheses:

a. Pneumonia is a clinical condition frequently complicating the nursing home stay of older persons;

Secondary hypotheses:

a. The onset of a pneumonia event in institutionalized older residents is associated with higher healthcare costs;

b. Incident pneumonia events are associated with an increased risk of mortality in older persons living in nursing home;

c. The onset of a pneumonia event is responsible for a significant worsening of the physical function of nursing home residents;

Tertiary hypotheses:

a. Specific variables at patient- and nursing home-level may predict the severity of the pneumonia-related functional loss;

b. Nursing home residents dying due to pneumonia produce a significantly higher burden in terms of healthcare costs compared to nursing home residents dying for other causes.

Therefore, the INCUR project will pursue the following aims:

Primary aims:

a. To estimate the incidence of pneumonia events in a sample of older nursing home persons over a period of 12 months;

Secondary aims:

a. To compare the healthcare costs of nursing home older persons experiencing a pneumonia event versus those who will not over a period of 12 months;

b. To calculate the mortality risk in a sample of older residents living in nursing home according to the presence/absence of a pneumonia event occurred during a follow-up period of 12 months;

c. To measure the physical function modifications experienced by a sample of nursing home residents according to the presence/absence of a pneumonia event occurred during a follow-up period of 12 months;

Tertiary aims:

a. To identify sociodemographic, clinical, and biological characteristics of nursing home older residents, as well as environmental and organizational factors of their own hosting institution, which are associated with a higher degree of functional loss following a pneumonia event;

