Each eligible participant will be followed-up for 12 months with a total of three clinical assessments: at baseline, 6 months (mid-term visit), and 12 months (close-out visit). The timeline of the INCUR project is depicted in Figure 1. Recruitment of participants and baseline visits began in February 2012 and ended in July 2012, after a preliminary organization phase (for coordinating activities of researcher with the participating nursing homes). The mid-term visit of participants (after 6 months of follow-up) is currently ongoing.

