### Physical function measures

Physical function modifications will be determined by repeated evaluations of several specific scales and questionnaires. In particular, we will use:

1. ADL scale [31]; The number of impaired ADLs was calculated considering the following six tasks: transferring from bed to chair, walking across a room, eating, bathing, using the toilet and personal hygiene.

2. IADL scale [32]; The assessment of impaired IADLs was based on the evaluation of the following four tasks: use of the telephone, use of transportations, managing medications and managing finances.

3. Short Physical Performance Battery (SPPB) [40,41]. The SPPB is a physical performance test composed by three timed subtasks: 4-meter usual gait speed, balance, and chair stand tests. Timed results from each test are scored from 0 (worst performers) to 4 (best performers) according to validated and standardized cut-points [41]. Participants unable to perform a specific SPPB subtest will result with a score of 0 (or the 99th percentile) for that part of the instrument. SPPB has shown to be associated with subclinical (e.g., inflammation, vitamin D, antioxidant status) [42,43] and clinical (e.g., comorbidity, disability, hospitalization, institutionalization, mortality) [44,45] in older persons;

4. Hand grip strength. It will be measured using a hand-held dynamometer (model Jamar). Participants will be asked to perform the task twice with each hand. The average of the best results obtained at each side will be used for the analyses. Hand grip strength has shown to be predictive of health-related events (including disability and mortality) [44,46-48];

5. *Groupes Iso-Ressources* (GIR). According to results of this scale, a special allowance (i.e., *Allocation Personalisée d'Autonomie*, APA) is allocated by the Conseil Général to functionally impaired subjects (scoring 4 or lower). Therefore, its significance is beyond a pure evaluation of physical function, but represents an easy and early indicator of the healthcare cost of an older person.

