c. When a pneumonia event will occur, physical function information collected after its onset will be compared to those previously recorded. The difference in physical function measured before and after the pneumonia event will be adjusted for the days between the event onset and the following physical function assessment. This analytical approach will allow to take into account the negative influence that the presence of a (sub)acute phase of the respiratory process may exert on physical function if the event will occur close to the evaluation. Mixed effects analysis of covariance models will also be performed to evaluate physical function modifications over time between patients who experienced a pneumonia event versus those who did not. If statistical power will be sufficient, stratified analyses will also be performed according to the severity of the pneumonia event (e.g., events requiring hospitalization versus those who did not).

For the present analyses, the sum of the results from the three SPPB categorized tests (ranging from 0 [worst physical performance] to 12 [best physical performance]) as well as the crude timed results obtained from each single assessment (in seconds) will be used for the analyses. This will allow to evaluate whether the pneumonia event will differently affect specific components of physical performance (i.e., balance, muscle strength, or gait/coordination).

Tertiary aims:

a. Chi-square and t-test analyses will be performed to describe the study population for main sociodemographic, behavioral, and clinical characteristics according to the presence/absence of a pneumonia event occurred during the INCUR project follow-up. Mann-Whitney U statistics will be used for non-normally distributed continuous variables. Normalization through log-transformation will be used for non-normally distributed study variables. Subsequent unadjusted and adjusted Cox proportional hazard models will be analyzed to identify patients’ characteristics that are able to significantly predict pneumonia events (dependent variable of interest). Among the covariates, age, gender, race, and preexisting respiratory conditions will always be considered as potential confounders. Age, gender, and race interactions will be tested for the studied relationships by adding specific interaction terms into the models. If possible, stratified analyses will be performed whereas significant interactions will be obtained.

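### The only comparison of physical function with non-cases groups residents by pneumonia at any time, so pre-event month-6 values enter the pneumonia group; separately, the inability rule leaves crude balance seconds open to a best-case value.

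*Protocol article*

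**What the plan says.** Hypotheses and objectives, secondary aim c, is to measure change in physical function "according to the presence/absence of a pneumonia event occurred during a follow-up period of 12 months". The Methods/design section sets assessments at baseline, 6 months and 12 months.

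Analysis plan, Secondary aims, c, gives two analyses:

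- Within residents who have an event, "physical function information collected after its onset will be compared to those previously recorded". The difference is "adjusted for the days between the event onset and the following physical function assessment".
- As an addition, a mixed effects analysis of covariance is to assess "physical function modifications over time between patients who experienced a pneumonia event versus those who did not". No time-updated exposure is stated for this model, and nothing links the onset date to the visits.

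The same paragraphs add that, besides the 0 to 12 SPPB sum, "the crude timed results obtained from each single assessment (in seconds) will be used for the analyses", in order to see whether balance, strength or gait is affected differently. Physical function measures, item 3, counts balance among the three timed subtasks and sets the rule for inability: "Participants unable to perform a specific SPPB subtest will result with a score of 0 (or the 99th percentile) for that part". It does not say which value goes with which subtest or scale.

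**The concern.** Aim c asks for a comparison by presence or absence of pneumonia. Nursing-home residents decline without pneumonia too, so the before/after analysis in cases alone cannot separate the event from background decline. The answer to aim c therefore rests on the mixed model. If a resident is labelled a case for the whole year, the month-6 value of someone infected in month 9 counts as pneumonia data although it precedes the infection. Whatever happened before the event, whether no change or an existing decline, is then attributed to pneumonia.

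The inability rule raises a second, smaller issue. A high percentile is a poor result where longer is worse, as in walking or chair-stand time. For a held stance longer is better, so the same percentile is a good result. Applied to crude balance seconds, it would make a resident who can no longer hold the stance look improved, in the analysis meant to isolate balance.

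**Working it through.** **The article's event counts.** From Sample size analyses: 22/2,140 × 365/28 × 800 = 107.2 events, and 107.2 × 0.8 × (0.5 + 0.5 × 0.6) = 68.6 in the worst case. Both reproduce. The article gives no effect size, SD or power for physical function, so what follows is expressed as a share of the true effect.

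**Share of first events after month 6.** Inputs:

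- Lower rate: 107.2/800 = 0.134 per resident-year, or 0.367 per 1,000 resident-days.
- Upper rate: 2.3 per 1,000 resident-days × 365 = 0.84 per year.
- Mortality of 20% per year, a hazard of −ln(0.8) = 0.223.

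With constant hazards and h = rate + 0.223, the share of first events in the second half-year is 1/(1 + exp(h/2)).

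- Lower rate: h = 0.357, share = 1/(1 + 1.196) = 0.455 (a simulation gave 0.45).
- Upper rate: h = 1.063, share = 1/(1 + 1.701) = 0.37.

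**Share of a true effect recovered under ever/never grouping.** Assume an immediate, lasting effect, equal background decline and complete follow-up. If a fraction f of cases is already post-event at month 6, the month-6 contrast recovers f, the average of months 6 and 12 recovers (f + 1)/2, and month 12 recovers all of it.

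| Timing of events | f (month 6) | Average of months 6 and 12 | Month 12 |
|---|---|---|---|
| Uniform | 50% | 75% | 100% |
| Constant rate, 0.134/yr | 54.5% | 77% | 100% |
| Constant rate, 0.84/yr | 63% | 81.5% | 100% |
| 40% fewer events in first half-year: 0.6/1.6 | 37.5% | 68.75% | 100% |
| 40% fewer events in second half-year: 1/1.6 | 62.5% | 81.25% | 100% |

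The 40% is the article's own seasonal reduction.

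**Fitted mixed models.** One simulated data set of 3,000 residents per scenario, true effect −1.0, complete follow-up:

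| Scenario | Month 6 | ANCOVA average | Month 12 | Post-event indicator |
|---|---|---|---|---|
| Uniform event times | −0.46 | −0.70 | −0.97 | −0.94 |
| 37.5% of events in first half-year | −0.32 | −0.63 | −0.93 | −1.02 |

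These are single data sets and carry sampling noise. With deaths simulated as well, the post-event indicator gave −1.19 and −0.84.

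**The opposite direction.** Take no true effect, but an assumed extra decline of 0.05 points per month in future cases. The expected false effect under fixed grouping is 0.05 × 6 = 0.30 at month 6 and 0.05 × 12 = 0.60 at month 12; the simulated values were −0.22 and −0.57. A simple post-event indicator still gave −0.43, so re-coding exposure cures the misplaced visits but not confounding by prior trajectory.

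**Balance seconds.** Assume a hold time capped at 10 s, with longer better (neither is stated in the article). The 99th percentile is then 10 s, the best possible value, where 0 s would be the worst. For assumed gait times the 99th percentile was 26.7 s against a median of 6.6 s, so there the rule marks a poor result as intended.

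**The case against.** The strongest reply is that the plan's first analysis for aim c is already anchored on onset and adjusted for time to the next assessment, with the mixed model as an addition. That is correct, and it would be wrong to say that ever/never grouping is the only way function is examined. But the first analysis has no non-cases, and the aim is worded as a comparison with them.

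A second reply is that a condensed article may leave exposure coding to a fuller document. This is possible. However, the aim defines the groups by an event during 12 months, and the cost and mortality analyses use the same two-group split, so the natural reading is a fixed grouping.

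A reader might infer that the bias always runs toward no effect. It does not: a month-12 contrast is nearly undiluted, and faster prior decline in future cases pushes the other way. Nor does the month-6 figure describe the planned model, which covers all visits.

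A reader might also infer that deaths after pneumonia invalidate the comparison. The article expects 20% mortality overall but gives nothing on how many cases would lack a post-event value, and missing outcomes are commonly left to the analysis plan.

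On the inability rule, the evident intent is a worst value and 0 is expressly allowed, so the article does not say that lost balance is scored as best. What stands is that it leaves that option open.

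**Conclusion.** The point holds in limited form and should be corrected. In the only comparison with non-cases, about 37 to 45% of cases would contribute a pre-event month-6 value as pneumonia data, given constant rates between 0.134 and 0.84 per year and 20% mortality. With an immediate, lasting effect and equal background decline, roughly 50 to 55% of the effect is recovered at month 6 (63% at the upper rate; 37.5 to 62.5% under the seasonal splits). About 75% is recovered when averaged over visits and nearly all at month 12. The direction is not fixed, since a steeper prior decline in future cases would produce exaggeration. The effect is on the interpretation of one secondary aim, not on the primary incidence estimate.

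The inability rule is an ambiguity that affects only crude balance seconds, and only if the percentile option is used there and a longer hold is better. The 0 to 12 SPPB sum is unaffected.

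**What to change.** In the mixed model of Secondary aims, c, define pneumonia as a time-updated exposure by visit interval (0 to 6 and 6 to 12 months) from the onset date, and keep non-cases as controls. Model end-of-interval function adjusted for start-of-interval function and, in exposed intervals, days since onset, with random effects for resident and nursing home. State how a later interval is coded after an event in the earlier one. Report the result as an association, since a steeper prior decline in future cases is not fully removed.

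In Physical function measures, item 3, replace the bracketed percentile option, for the crude-seconds analyses, with a worst value for each subtest: the 99th-percentile time for gait and chair stand, and 0 seconds for balance. Keep 0 points for the SPPB score.

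The cost is a few sentences. Onset and visit dates are already needed for the planned before/after adjustment, so no new data are required.
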